#### Participant timeline

The data collection timeline is represented in table 8. The collection of secondary outcomes throughout follow-up is also performed for patients who have died before its completion time point (ie, at 3 months after ICU discharge), as applicable.

**Table 8 T8:** Summary presentation of data collection schedule

	Visit 1 study inclusion	Visit - teleconsultation	Visit 2 ICU discharge*	Visit 3 follow-up 3 months post-ICU discharge	
Control phase (CP) Intervention phase (IP)	CP/IP	IP	CP/IP	CP/IP	
Time (hours; days (d))	Any time after 72 hours	<48 hours after inclusion		28 d after ICU discharge (retrospective)	90 d after ICU discharge
Review of inclusion and exclusion criteria, medical history	x				
Information/declaration of consent by legally recognised, substitute decision-maker	x				
Information/declaration of consent by patient	x				
Primary endpoint (ICU length of stay)	x		x		
Secondary endpoints	x	x	x	x	x
Mortality	x	x	x	x	x

* Defined as the last day of ICU stay (ie, the day of occurrence of ICU discharge that is not followed by any ICU readmission during the index hospitalisation); in case of more than one ICU admission during the index hospitalisation, the data on secondary endpoints are (repeatedly) collected on the corresponding days of ICU discharge; however, only the data collected on the last one of the aforementioned ICU discharge days are included in the secondary endpoints’ analyses.

ICU, intensive care unit.

### Sample size calculation

Primary endpoint is ICU LOS in days. We originally planned to recruit 23 ICUs for the trial, each recruiting two to three patients on average per month. Over the trial period of 35 months (including a crossover month without recruitment), we expected each ICU to recruit at least n=87 patients, resulting in at least n=23×87=2001 patients throughout the trial period. Assuming an average ICU LOS of 9 days during the control phase, a sample size of n=2001 patients in the trial would have yielded a power of approximately 85% at a two-sided significance level of 5% to detect a difference in ICU LOS between the intervention and control group of −2 days (SD±9 days).

This calculation was based on simulations using an intracluster correlation coefficient of 0.01 and various possible recruitment schemes with 2–3 average patients recruited per month per ICU. Reducing ICU LOS by 2 days means a clinically relevant reduction of burden by treatment and suffering of patients and their families. The calculations were performed with the software package R (V.4.1.2)^34^ and the programme package swCRTdesign (V.4.0).^35^

During the study initiation phase, 28 ICUs had confirmed participation. To mitigate potential cross-talk between ICUs located within the same institution, we grouped those sharing the same postal address into clusters. As a result, we randomised the crossover time point for each cluster (see online supplemental material figure 1A). Power calculations for this setup indicated an average statistical power of 85% for detecting the expected effect on ICU LOS.

Several months after initiation, two ICUs had dropped out because of delay in contract finalisation or non-recruitment. One ICU was replaced and additional in-house ICU units were added. In July 2025, it was decided to extend the control phase of clusters that had not yet transitioned into the intervention phase by 1 month, without extending the overall study duration of 35 months. This decision was made to mitigate recruitment delays during the control phase and reduce the associated design imbalance between the control and intervention groups. Based on the current recruitment rates and the initial planning assumptions, this modification would conservatively result in a power of approximately 80% at a two-sided significance level of 5% (see online supplemental material figure 1B for the adjusted study design chart).

### Patient recruitment and assignment of interventions

All consecutive patients and their next-of-kin fulfilling the eligibility criteria are invited to participate. The informed consent process is detailed below. Patient data are entered by on-site study personnel into the eCRF in secuTrial, which was set up by the Charité Clinical Trials Office.

Randomisation has been performed at the cluster level. Each cluster has been randomly assigned a time point for transitioning to the intervention phase during a crossover month, resulting in a permuted order of all clusters. The randomisation list was generated by the Institute of Biometry and Clinical Epidemiology of Charité-Universitätsmedizin Berlin using the R software package via random sampling without replacement.

### Data collection and management

#### Data collection and trial procedures during ICU stay and follow-up

Collected variables are summarised in figure 1 and tables1^8^; additional details are provided in the online supplemental material 7.

#### ICU treatment

Data documented by local research teams for all patients while in ICU include:

Baseline data and critical illness characteristics (date and mode of hospital and ICU admission, ICU admission cause/diagnosis, eligibility criteria, documented pre-existing conditions/medical history, illness severity scores).Symptom burden (psychological, physical, social and spiritual) in the context of specialised PC consultation (intervention period only).HRQoL.ICU clinical course data (complications, organ replacement therapy, highest sequential organ dysfunction assessment score, delirium assessment/duration, treatment limitations).Hospital and ICU discharge data (discharge destination (intermediate care/normal care/death) and date).Patient details (unique identifiers, sociodemographic information, health insurance status).

#### Follow-up procedures and postacute care

Follow-up data are collected during a telephone interview with surviving patients and/or patients’ relatives, including HRQoL, use of health services and resources, satisfaction with care, symptom control, communication and decision-making, and perceived facilitators of and barriers to PC; the latter have been previously determined through research performed by the department of anesthesiology and intensive care, Lillebaelt University Hospital, Region of Southern Denmark. Survival status is determined at 3 months after ICU discharge from the patient, their relatives, general practitioner or municipal records/databases.

#### Medical resource use, cost and reimbursement data

Patient-level cost and billing data will be provided by the administrations of participating hospitals. Variables collected at the patient level will cover real costs of healthcare and reimbursements invoiced (including flat-fee reimbursement codes if applicable), between the start of the index hospitalisation and 3-month follow-up (see online supplemental material 8, figure 2).

Medical resource use data, including relevant admission and discharge dates, and information on informal care and resulting productivity losses are collected or extracted from clinical information systems by study staff (until the end of index hospitalisation) or self-reported by patients and relatives (from index hospitalisation’s end to the 3-month follow-up time point). This information will be combined with unit costs either stemming from publicly accessible, external sources or also provided by the hospital administrations. Centre-level unit costs requested from the hospital administrations will include, among others, average daily costs for an ICU, intermediate care or normal ward stay. Additionally, costs related to mechanical ventilation, renal or liver replacement and extracorporeal life support are collected, as well as different types of overhead expenses and salary levels (eg, ICU nurse, ICU physician, PC specialist).

The costs of the intervention will be estimated considering the cost of telemedicine technology (based on information from centres and/or technology providers), staff time (for training, PC consultations) and staff costs per unit of time, by relevant profession. The required information will be covered by the study data collection or provided anonymously/at the hospital level by the centres.

#### Data management

All clinical data collected during the study are stored in a bespoke secuTrial database (interactive Systems GmbH, Berlin, Germany) hosted by Charité-Universitätsmedizin Berlin and directly analysed from this database. Further details on data management, pseudonymisation and the data handling are provided in online supplemental material 9.

### Statistical methods

The statistical evaluation will be conducted by the Institute of Biometry and Clinical Epidemiology, Charité-Universitätsmedizin Berlin. Health economics analyses will be conducted by the Institute of Pharmaceutical Medicine and health economics facility, department of public health, University of Basel.

#### Data analysis plan

A detailed Statistical Analysis Plan will be finalised before database lock. The analysis of the data will begin with a detailed statistical description of the study sample, differentiated by control and intervention phase. Categorical characteristics will be summarised using absolute and relative frequencies. For ordinal or metric non-normally distributed data with up to five categories, we will present the absolute and relative frequencies, along with the median and the IQR. For data with more than five categories, only the median and IQR will be reported. For metric data that follows a normal distribution, we will present the mean value, accompanied by the SD and the 95% CI.

All analyses will be conducted on an intention-to-treat basis, with the patient representing the unit of analysis. We will use generalised linear mixed models (GLMMs) for continuous outcomes,^23 35^ accounting for the clustered data structure, to compare the primary endpoint between the control and intervention phases. Sensitivity analyses will include additional adjustment for ICU mortality.

Predefined subgroup analyses will be conducted to explore the heterogeneity of the treatment effect in patients concerning sex, religiosity, socioeconomic parameters and educational level. In addition, treatment effects will be compared between ICUs with high-tech versus low-tech telemedicine consultations, with good versus average or poor ethical climate, and ICUs with and without pre-existing palliative counselling. Further comparisons will be made among participating countries, patients with an ICU stay at enrolment of less than 5 days versus at least 5 days, and patients with versus without decisions to limit treatment at enrolment.

Subgroup analyses and analyses of all secondary endpoints will be considered as exploratory. Statistical testing will be carried out at a two-sided significance level of 5%. For the primary hypothesis, no correction for multiple testing is necessary.

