### Objectives and hypotheses

The study will address the following specific objectives:

Clinical outcomes: assess the impact of the complex intervention on ICU LOS, the duration of mechanical ventilation and other organ replacement interventions and the proportion of patients with limitations of life-sustaining therapies.Quality of life: assess the impact of the intervention on health-related quality of life (HRQoL).Economic evaluation: estimate impact on resource use, analyse cost implications and determine the cost-effectiveness and cost–consequence situation of the intervention.Perception of care: evaluate whether patients and their relatives experience improved care quality and communication in the ICU, particularly in relation to end-of-life care and symptom management.Staff well-being: examine whether ICU clinicians (both physicians and nurses) report fewer stressors and perceive an improved ethical decision-making climate and practice.

The primary hypothesis is that the complex intervention will reduce the average ICU LOS by at least 2 days compared with standard care before. Secondary hypotheses include an increase in treatment limitation decisions; improved economic efficiency; enhanced perceived quality of care (notably in symptom management and shared decision-making); an improvement in HRQoL among survivors; and ameliorated moral distress among ICU clinicians.

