### Outcome measures

#### Primary outcome

The primary outcome is the ICU LOS in days, operationalised as the total number of consecutive and/or non-consecutive ICU days from the start to the end of an index hospitalisation at a study-participating hospital; any transfer to another hospital for treatment continuation signifies termination of the index hospitalisation, and therefore, any subsequent ICU admission cannot contribute to the measured ICU LOS. Regarding index hospitalisation, whenever ICU discharge is followed by ICU readmission on the same day, ICU LOS is determined by taking into account the aforementioned day only once (rather than two times).

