#### Secondary outcomes

Secondary outcomes are collected up to 3 months after the last day of ICU stay (ie, the day of ICU discharge that is not followed by any ICU readmission during the index hospitalisation); they are listed in tables1^7^.

**Table 1 T1:** Clinical outcome measures (hospital stay)

Outcome measure	Measure description	Time frame
Maximum SOFA Score	Maximum sepsis-related organ failure assessment score, including a derived delta SOFA (total maximum SOFA minus admission SOFA) as a descriptor of multiple organ dysfunction.	During ICU stay (average ~7–9 days)
Incidence of delirium	Occurrence of delirium measured by validated delirium scoring instruments.	During ICU stay (average ~7–9 days)
ICU complications	Occurrence of any complication impacting length of stay and mortality. Captured by the question: CPR, tracheostomy, major surgery due to complication or none.	During ICU stay (average ~7–9 days)
Presence and nature of treatment limitations	Documentation of treatment limitations (eg, restrictions on frequency, scope or duration of interventions).	During ICU stay (average ~7–9 days)
ICU mortality (yes/no)	Whether the patient died during the ICU stay.	During ICU stay (average ~7–9 days)
Readmissions to ICU	The frequency at which patients, after being transferred out of the ICU, are readmitted to the ICU.	During hospital stay (expected average ~14–16 days)
Length of hospital stay	Total number of days from hospital admission to hospital discharge.	During hospital stay (expected average ~14–16 days)
Discharge destination (ICU)	Recorded destination on ICU discharge. Options include: hospital unit, other ICU in the hospital, external ICU, skilled nursing facility, rehabilitation unit, palliative care unit, hospice, home or other.	During hospital stay (expected average ~14–16 days)
Discharge destination (hospital)	Recorded destination on hospital discharge. Options include: skilled nursing facility, rehabilitation unit, palliative care unit, hospice, home or other.	During hospital stay (expected average ~14–16 days)
Hospital mortality (yes/no)	Whether the patient died during the overall hospital stay.	During hospital stay (expected average ~14–16 days)
Days of mechanical ventilation	Total number of days the patient received invasive mechanical ventilation.	During ICU/hospital stay
Days of ECMO	Total number of days the patient was supported by ECMO.	During ICU stay

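### Adjusting ICU length of stay for ICU mortality conditions on a post-intervention outcome: it is biased if the intervention affects ICU death, and it cannot tell earlier death from faster discharge alive

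*Protocol article*

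**What the plan says.** The endpoint is a count of days over the index hospitalisation: "The primary outcome is the ICU LOS in days, operationalised as the total number of consecutive and/or non-consecutive ICU days" (Primary outcome). The definition says how transfers are treated ("any transfer to another hospital for treatment continuation signifies termination of the index hospitalisation") but gives no separate treatment to a stay that ends in death.

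The primary analysis is a mixed model, "accounting for the clustered data structure, to compare the primary endpoint between the control and intervention phases", with no mortality term stated. The same paragraph of the Data analysis plan then fixes one further analysis: "Sensitivity analyses will include additional adjustment for ICU mortality".

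ICU mortality is listed in Table 1 among the secondary outcomes, as "Whether the patient died during the ICU stay". Table 8 places the teleconsultation "<48 hours after inclusion", so for most patients the intervention comes before ICU death or discharge. Two routes from intervention to ICU death are visible in the article. One is stated as an expectation: "Secondary hypotheses include an increase in treatment limitation decisions" (Objectives and hypotheses). The other is the place of death, since the recorded ICU discharge destinations in Table 1 include "skilled nursing facility, rehabilitation unit, palliative care unit, hospice, home or other".

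**The concern.** Death in the ICU ends the stay, so an early death counts as a short stay. A natural question about any fall in mean stay is whether patients left the ICU alive sooner or died sooner. The Discussion describes the aim as a shorter stay with no harm to survival, so the answer governs how a positive result is read.

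Putting ICU death into the model as a covariate does not answer this, for two separate reasons.

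1. ICU death is a possible consequence of the intervention, not a baseline confounder. If the intervention changes who dies in the ICU, or moves some deaths elsewhere, the ICU survivors in the two phases are different kinds of patient. So are the decedents. Comparing within these groups then distorts the phase contrast.
2. A yes/no indicator says nothing about when death occurred. If the same patients die, only sooner, the covariate is balanced between phases and leaves the estimate where it was.

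At stake is the reading of the result: agreement between the crude and adjusted estimates could be taken as evidence that death does not explain the reduction.

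**Working it through.** **Inputs from the article.** Control mean stay 9 days, target difference -2 days, SD 9, intracluster correlation 0.01, 23 ICUs x 87 patients = 2001, 35 months, two-sided 5%, power about 85% (Sample size calculation).

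**Inputs assumed.** The article gives no ICU mortality for the enrolled population and no stay by survival status. The checks use 40% ICU mortality in the control phase, phases of equal size, and splits that keep the overall mean at 9 days: decedents 12 and survivors 7 (0.4 x 12 + 0.6 x 7 = 9.0), or the mirror image, 6 and 11 (0.4 x 6 + 0.6 x 11 = 9.0).

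**The plan's own figure, as a scale.** A stepped-wedge variance with month effects and a random cluster intercept, 87/34 = 2.56 patients per ICU per month, and crossovers assumed in months 7 to 29, gives 83.7% power, close to the stated 85%. The true schedule is in a supplement not shown; other assumed windows give 65% to 93%. A power of 85% for 2 days implies a standard error of about 2/(1.960 + 1.036) = 0.67 days.

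**Formula.** In a linear model of stay on phase and ICU death, the adjusted phase effect is the average of the differences within decedents and within survivors, with weights n0 x n1/(n0 + n1). Clustering and period are left out for clarity.

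**Check 1: timing.**
- ICU mortality 40% in both phases, deaths 5 days sooner, survivors unchanged. Crude: 0.40 x (-5) = -2.0. Weights per 100 patients per phase: decedents 40 x 40/80 = 20, survivors 60 x 60/120 = 30. Adjusted: (20 x (-5) + 30 x 0)/50 = -2.0.
- Deaths unchanged, survivors leave 3.33 days sooner. Crude: 0.60 x (-3.33) = -2.0. Adjusted: (20 x 0 + 30 x (-3.33))/50 = -2.0.

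The two mechanisms give the same crude and the same adjusted estimate.

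**Check 2: a shift in place of death, with nobody's stay changed.** Ten of the 40 points of ICU deaths become same-day transfers to hospice, so ICU deaths are 40 versus 30 and ICU survivors 60 versus 70. Weights: 40 x 30/70 = 17.14 and 60 x 70/130 = 32.31. With the 12/7 split, the intervention-phase survivor mean is (0.6 x 7 + 0.1 x 12)/0.7 = 7.71, a difference of 0.714. Decedents do not differ. Adjusted: 32.31 x 0.714/(17.14 + 32.31) = +0.47 days. The crude and true effects are 0. The same formula for smaller shifts:

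| Shift in ICU deaths | Weights (decedents, survivors) | Survivor difference | Adjusted, 12/7 split | Adjusted, 6/11 split |
|---|---|---|---|---|
| 10 points | 17.14, 32.31 | 0.714 | +0.47 | -0.47 |
| 5 points | 18.67, 31.20 | 0.385 | +0.24 | -0.24 |
| 2 points | 19.49, 30.49 | 0.161 | +0.10 | -0.10 |

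**Check 3: simulation.** One million patients in two groups, control mean about 9 days, control ICU mortality about 38%, and severity affecting both stay and death.

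| Scenario | ICU mortality, control to intervention | True effect | Adjusted |
|---|---|---|---|
| No effect on stay or death | 38% to 38% | 0.00 | 0.00 |
| Same deaths, sooner | 38% to 38% | -2.00 | -2.01 |
| Survivors discharged sooner | 38% to 38% | -2.00 | -1.99 |
| Reduction comes entirely from extra ICU deaths | 38% to 47% | -1.69 | -2.03 |
| Stay unchanged, some deaths move out of the ICU | 38% to 29% | 0.00 | +0.35 |
| Stay unchanged, long-stay survivors become ICU deaths | 38% to 47% | 0.00 | -0.49 |

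In the fourth row adjustment enlarges the apparent benefit instead of removing it.

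**The case against.** Several stronger readings are tempting, and the document does not support them.

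- **That the adjusted analysis is biased in any case.** It is not. If the intervention leaves ICU death unaffected, the bias is zero. The article cites literature in which overall mortality did not change. A shift in ICU death is plausible from the expected treatment limitations and the discharge destinations, but the article does not quantify one.
- **That Check 1 demonstrates bias from adjustment.** It does not. Total ICU days over all patients is the defined endpoint, and -2.0 is its true change. The ambiguity belongs to mean stay itself and remains if the covariate is removed. What Check 1 shows is that the covariate does not resolve it.
- **That the size is established.** The mortality level, the splits and the switching patterns are assumptions, and they also set the sign. Moving 10 of 40 points is a large shift, and even then 0.47 days is 0.47/0.67 = 0.7 of a standard error.
- **That the article otherwise ignores death.** ICU and hospital mortality, treatment limitations and discharge destination are secondary outcomes, and survival status is determined at 3 months. These show whether and where patients died. They need not reveal earlier death: in Check 1 ICU mortality is 40% in both phases. The list of sensitivity analyses is also open-ended and an SAP is to follow, so the absence of another method from the article is not itself a fault.
- **That the article will present agreement as proof of robustness.** It states no purpose for this analysis. That use is a risk, not a commitment.

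What stands is narrower: the one sensitivity analysis that is named conditions on a post-intervention outcome and cannot separate the two mechanisms.

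**Conclusion.** The point holds with its condition attached. The mortality-adjusted contrast is biased whenever the intervention changes who dies in the ICU or where. Under the assumed 40% mortality and the 12/7 or 6/11 splits, the bias is about 0.1 to 0.5 days in either direction for a 2 to 10 point shift, and nil without a shift. The failure to distinguish earlier death from faster discharge alive needs no such condition: with ICU mortality equal in both phases, a full 2-day reduction produced by earlier death passes through the adjustment unchanged.

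Severity is moderate. A reader might infer that the trial's main result is compromised, but the primary mixed model carries no stated mortality term, so its estimate, test and power are untouched. The harm lies in relying on this sensitivity analysis as evidence that deaths do not explain a shorter stay.

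**What to change.** In the SAP, which is to be finalised before database lock:

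1. Drop the mortality-adjusted model. If it is kept, state that it conditions on a post-intervention outcome and will not be read as ruling out a reduction through death.
2. Prespecify a competing-event analysis of time to final ICU discharge alive versus ICU death: cause-specific hazards and cumulative incidence, with cluster and period terms. Treat transfer to another hospital as a separate event type. That agrees with the endpoint definition, whereas censoring transfers would depart from it and may be informative. State a rule for readmissions within the index hospitalisation, because the endpoint counts non-consecutive days. State the time origin, because patients are enrolled at any time after 72 hours.
3. Show stay separately for ICU survivors and ICU decedents, as description only.
4. Add days alive and outside the ICU only over the index hospitalisation, or another horizon for which death dates and ICU days are collected. The article does not show that a 3-month horizon is covered: Table 5 lists rehospitalisations by number and/or total days without ICU days, and the follow-up section gives survival status, not date of death.

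For items 1 to 3 the cost is SAP wording and a few extra models; admission and discharge dates and discharge destination, including death, are already recorded. The downside is that a time-to-event result estimates something different from mean total ICU days, so it supplements the primary estimate and does not re-estimate it.
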